**Table B. Guidelines for Physical Examination**

| **Dehydration** | Assess skin touch and turgor, mucous membranes, eyes, crying, fontanelle, pulse, urine output |
| --- | --- |
| **Jaundice** | Assess for yellowing of the sclera. Also evaluate the palpebral conjunctiva, lips, and skin. |
| **Chest** | Observe the rate, rhythm, depth, and effort of breathing. Check the patient’s colour for cyanosis.  The maximum acceptable respiratory rate by age: < 2 months = 60, 2-12 months = 50, 1-5 years = 40, above 5 years = 30.  Inspect the neck for the position of the trachea, for supraclavicular retractions, and for contraction of the sternomastoid or other accessory muscles during inspiration.  Auscultate the anterior and posterior chest for normal breath sounds and any adventitious sounds (crackles or rales, wheezes, and rhonchi). *Crackles are intermittent, non-musical, fine or coarse sounds that may be due to abnormalities of the lungs (pneumonia, fibrosis, early congestive heart failure) or airways (bronchitis or bronchiectasis). Wheezes are high-pitched and result from narrowed airways. Rhonchi are relatively low-pitched and suggest secretions in large airways.*  If abnormalities are identified, evaluate for transmitted voice sounds. In addition, palpate the chest to assess for tactile fremitus, and percuss the chest to assess for areas of dullness*. Normal, air-filled lungs emit predominantly vesicular breath sounds, transmit voice sounds poorly with “ee” = “ee”, and have no tactile fremitus. Airless lung, as in lobar pneumonia, emits bronchial breath sounds, transmits spoken words clearly with “ee” = “aay” (egophany), and has an increase in tactile fremitus.* |
| **Abdomen** | Inspect and ausculate the abdomen. Listen for bowel sounds in the abdomen before palpating it. Palpate the abdomen in all 4 quadrants lightly and then deeply. Assess the size of the liver and spleen. To assess for peritoneal inflammation, look for localised and rebound tenderness, and voluntary or involuntary rigidity. |
| **Skin** | Inspect the skin for colour, turgor, moisture, and lesions. If lesions are present, note their location and distribution (diffuse or localised), arrangement (linear, clustered, annular, dermatomal), type (macules, papules, vesicles) and colour. |
| **Tablet test** | For children > 9 months of age, ask the patient to pick a tablet (or equivalent object) up off a flat surface using the thumb and index finger of their dominant hand*. This tests for co-ordination of the upper extremity assessing the function of the motor system, cerebellar system, vestibular system (for coordinating eye and body movements) and the sensory system, for position sense. When testing small children, be aware that they will likely attempt to put the object into their mouth.* |

**Table C. Grading Physical Examination Findings**

|  | **Grade 1**  **MILD** | **Grade 2**  **MODERATE** | **Grade 3**  **SEVERE** | **Grade 4**  **LIFE-THREATENING** |
| --- | --- | --- | --- | --- |
| **Temperature* (axillary)** | 37.5-37.9C | 38.0-39.5C | > 39.5C | Sustained fever, equal or greater than 40.0C for longer than 5 days |
| **Dehydration** | Less than 2 of the following:  Restless, irritable  Sunken eyes  Drinks eagerly, thirsty  Skin pinch goes back slowly | 2 of the following:  Restless, irritable  Sunken eyes  Drinks eagerly, thirsty  Skin pinch goes back slowly | Two of the following:  Lethargic or unconscious  Sunken eyes  Not able to drink or drinking poorly  Skin pinch goes back very poorly | Two of the following + shock:  Lethargic or unconscious  Sunken eyes  Not able to drink or drinking poorly  Skin pinch goes back very poorly |
| **Jaundice** | Slight yellowing of sclera and conjunctiva | Moderate yellowing of sclera and conjunctiva, yellowing of mucous membranes | Severe yellowing of sclera and conjunctiva, yellowing of skin | N/A |
| **Chest** | Mildly increased RR (for age, temperature), transient or localised adventitious sounds | Moderately increased RR, diffuse or persistent adventitious sounds | Rapid RR (< 2 months > 60, 2-12 months > 50, 1-5 years > 40, adults > 30)* nasal flaring, retractions | Cyanosis |
| **Abdomen** | Normal bowel sounds, mild localised tenderness, and/or liver palpable 2-4 cm below the right costal margin (RCM), and/or spleen palpable, and/or umbilical hernia present | Normal or mildly abnormal bowel sounds, moderate or diffuse tenderness; and/or mild to moderately enlarged liver (4-6 cm below the RCM) and/or spleen palpable up to half-way between umbilicus and symphysis pubis | Severely abnormal bowel sounds, severe tenderness to palpation. Evidence of peritoneal irritation and/or significant enlargement of liver (> 6 cm below the RCM) and/or spleen palpable beyond half-way between umbilicus and symphysis pubis | Absent bowel sounds. Involuntary rigidity |
| **Skin†** | Localised rash, erythema, or pruritis | Diffuse, maculopapular rash, dry desquamation | Vesiculation, moist desquamation, or ulceration | Exfoliative dermatitis, mucous membrane involvement or erythema multiforme or suspected Stevens-Johnson or necrosis requiring surgery |

|  | **Grade 1**  **MILD** | **Grade 2**  **MODERATE** | **Grade 3**  **SEVERE** | **Grade 4**  **LIFE-THREATENING** |
| --- | --- | --- | --- | --- |
| **Hearing** | *< 4 years: N/A*  > 4 years: Decreased hearing in one ear | *< 4 years: N/A*  > 4 years: Decreased hearing in both ears or severe impairment in one ear | *< 4 years: Any evidence of hearing impairment*  > 4 years: Severe impairment in both ears | N/A |
| **Tablet test** | Difficulty grasping tablet but able to pick up | Unable to pick up tablet without dropping | Unable to grasp tablet | N/A |
| **Clinical symptoms / sign *(not otherwise specified)*** | No treatment required; monitor condition | Treatment required | Requires treatment and possible hospitalisation | Requires active medical intervention, hospitalisation, or hospice care |

Reference – The Harriet Lane Handbook, 15th edition, 2000

† Reference – WHO Toxicity Grading Scale for Determining the Severity of Adverse Events

**TABLE D. Guidelines for Grading of Laboratory Abnormalities**

|  | **Grade 1**  **MILD** | **Grade 2**  **MODERATE** | **Grade 3**  **SEVERE** | **Grade 4**  **LIFE-THREATENING** |
| --- | --- | --- | --- | --- |
| **Haemoglobin**  ***(****g/dL)* | 9.0 – 9.9 | 7.0 – 8.9 | 5.0 – 6.9 | < 5.0 |

Reference – The Harriet Lane Handbook, 15th edition, 2000†

Reference – WHO Toxicity Grading Scale for Determining the Severity of Adverse Events

**APPENDIX II**

**Table A. Dihydroartemisinin will be given daily. The number of tablets per day is reported in brackets. One tablet of Artekin (pediatric tablets) contains 20/40 mg of DHA and 160/320 mg of PPQ..**

| **Weight in kg** | **mg of DHA to be given daily** | **Dose of DHA as mg/kg/d** |
| --- | --- | --- |
| 4 - 6 | 10 (1/2 tablet with 20 mg) | 1.67 - 2.5 |
| 7 - 12 | 20 (1 tablet with 20 mg) | 1.67 - 2.86 |
| 13 - 23 | 40 (1 tablet with 40 mg) | 1.74 - 3.08 |
| 24 - 35 | 80 (2 tablets with 40 mg) | 2.29 - 3.33 |
| 36 - 75 | 120 (3 tablets with 40 mg) | 1.6 - 3.64 |

*One tablet of Artekin contains 40 mg of DHA and 320 mg of PPQ for adult patients.*

**Table B: Piperaquine will be given daily. The number of tablets per day is reported in brackets. One tablet of Artekin (pediatric tablets) contains 20/40 mg of DHA and 160/320 mg of PPQ.**

| **Weight in kg** | **mg of PPQ to be given daily** | **Dose of PPQ as mg/kg/d** |
| --- | --- | --- |
| 4 - 6 | 80 (1/2 tablet with 160 mg) | 13.36 - 20 |
| 7 - 12 | 160 (1 tablet with 160 mg) | 13.36 – 22.88 |
| 13 - 23 | 320 (1 tablet with 320 mg) | 13.92 – 24.64 |
| 24 - 35 | 640 (2 tablets with 320 mg) | 18.32 – 26.4 |
| 36 - 75 | 960 (3 tablets with 320 mg) | 12.8 – 29.12 |

*One tablet of Artekin contains 40 mg of DHA and 320 mg of PPQ for adult patients.*

**Table C: Coartem® dose based on boy weight will be given daily. Tablets containing 20 mg of Artemether and 120 mg of Lumefantrine.**

| **Weight in kg** | **Number of tablet per dose** |
| --- | --- |
| 5 to < 15 kg | 1 tablet per dose |
| 15 to < 25 kg | 2 tablets per dose |
| 25 to < 35 kg | 3 tablets per dose |

**APPENDIX III**

**WORLD MEDICAL ASSOCIATION DECLARATION OF HELSINKI**

**Ethical Principles for Medical Research Involving Human Subjects**

**Recommendations guiding medical physicians**

**in biomedical research involving human subjects**

Adopted by the 18th WMA General Assembly

Helsinki, Finland, June 1964

and amended by the

29th WMA General Assembly, Tokyo, Japan, October 1975

35th WMA General Assembly, Venice, Italy, October 1983

41st WMA General Assembly, Hong Kong, September 1989

48th WMA General Assembly, Somerset West, Republic of South Africa, October 1996

and the

52nd WMA General Assembly, Edinburgh, Scotland, October 2000

Note of Clarification on Paragraph 29 added by the WMA General Assembly, Washington 2002.

**A. INTRODUCTION**

1. The World Medical Association has developed the Declaration of Helsinki as a statement of ethical principles to provide guidance to physicians and other participants in medical research involving human subjects. Medical research involving human subjects includes research on identifiable human material or identifiable data.

2. It is the duty of the physician to promote and safeguard the health of the people. The physician's knowledge and conscience are dedicated to the fulfillment of this duty.

3. The Declaration of Geneva of the World Medical Association binds the physician with the words, "The health of my subject will be my first consideration," and the International Code of Medical Ethics declares that, "A physician shall act only in the subject's interest when providing medical care which might have the effect of weakening the physical and mental condition of the subject."

4. Medical progress is based on research which ultimately must rest in part on experimentation involving human subjects.

5. In medical research on human subjects, considerations related to the well-being of the human subject should take precedence over the interests of science and society.

6. The primary purpose of medical research involving human subjects is to improve prophylactic, diagnostic and therapeutic procedures and the understanding of the etiology and pathogenesis of disease. Even the best proven prophylactic, diagnostic, and therapeutic methods must continuously be challenged through research for their effectiveness, efficiency, accessibility and quality.

7. In current medical practice and in medical research, most prophylactic, diagnostic and therapeutic procedures involve risks and burdens.

8. Medical research is subject to ethical standards that promote respect for all human beings and protect their health and rights. Some research populations are vulnerable and need special protection. The particular needs of the economically and medically disadvantaged must be recognized. Special attention is also required for those who cannot give or refuse consent for themselves, for those who may be subject to giving consent under duress, for those who will not benefit personally from the research and for those for whom the research is combined with care.

9. Research Investigators should be aware of the ethical, legal and regulatory requirements for research on human subjects in their own countries as well as applicable international requirements. No national ethical, legal or regulatory requirement should be allowed to reduce or eliminate any of the protections for human subjects set forth in this Declaration.

**B. BASIC PRINCIPLES FOR ALL MEDICAL RESEARCH**

10. It is the duty of the physician in medical research to protect the life, health, privacy, and dignity of the human subject.

11. Medical research involving human subjects must conform to generally accepted scientific principles, be based on a thorough knowledge of the scientific literature, other relevant sources of information, and on adequate laboratory and, where appropriate, animal experimentation.

12. Appropriate caution must be exercised in the conduct of research which may affect the environment, and the welfare of animals used for research must be respected.

13. The design and performance of each experimental procedure involving human subjects should be clearly formulated in an experimental protocol. This protocol should be submitted for consideration, comment, guidance, and where appropriate, approval to a specially appointed ethical review committee, which must be independent of the Investigator, the Sponsor or any other kind of undue influence. This independent committee should be in conformity with the laws and regulations of the country in which the research experiment is performed. The committee has the right to monitor ongoing trials. The researcher has the obligation to provide monitoring information to the committee, especially any serious adverse events. The researcher should also submit to the committee, for review, information regarding funding, Sponsors, institutional affiliations, other potential conflicts of interest and incentives for subjects.

14. The research protocol should always contain a statement of the ethical considerations involved and should indicate that there is compliance with the principles enunciated in this Declaration.

15. Medical research involving human subjects should be conducted only by scientifically qualified persons and under the supervision of a clinically competent medical person. The responsibility for the human subject must always rest with a medically qualified person and never rest on the subject of the research, even though the subject has given consent.

16. Every medical research project involving human subjects should be preceded by careful assessment of predictable risks and burdens in comparison with foreseeable benefits to the subject or to others. This does not preclude the participation of healthy volunteers in medical research. The design of all studies should be publicly available.

17. Physicians should abstain from engaging in research projects involving human subjects unless they are confident that the risks involved have been adequately assessed and can be satisfactorily managed. Physicians should cease any investigation if the risks are found to outweigh the potential benefits or if there is conclusive proof of positive and beneficial results.

18. Medical research involving human subjects should only be conducted if the importance of the objective outweighs the inherent risks and burdens to the subject. This is especially important when the human subjects are healthy volunteers.

19. Medical research is only justified if there is a reasonable likelihood that the populations in which the research is carried out stand to benefit from the results of the research.

20. The subjects must be volunteers and informed participants in the research project.

21. The right of research subjects to safeguard their integrity must always be respected. Every precaution should be taken to respect the privacy of the subject, the confidentiality of the subject's information and to minimize the impact of the study on the subject's physical and mental integrity and on the personality of the subject.

22. In any research on human beings, each potential subject must be adequately informed of the aims, methods, sources of funding, any possible conflicts of interest, institutional affiliations of the researcher, the anticipated benefits and potential risks of the study and the discomfort it may entail. The subject should be informed of the right to abstain from participation in the study or to withdraw consent to participate at any time without reprisal. After ensuring that the subject has understood the information, the physician should then obtain the subject's freely-given informed consent, preferably in writing. If the consent cannot be obtained in writing, the non-written consent must be formally documented and witnessed.

23. When obtaining informed consent for the research project the physician should be particularly cautious if the subject is in a dependent relationship with the physician or may consent under duress. In that case the informed consent should be obtained by a well-informed physician who is not engaged in the investigation and who is completely independent of this relationship.

24. For a research subject who is legally incompetent, physically or mentally incapable of giving consent or is a legally incompetent minor, the Investigator must obtain informed consent from the legally authorized representative in accordance with applicable law. These groups should not be included in research unless the research is necessary to promote the health of the population represented and this research cannot instead be performed on legally competent persons.

25. When a subject deemed legally incompetent, such as a minor child, is able to give assent to decisions about participation in research, the Investigator must obtain that assent in addition to the consent of the legally authorized representative.

26. Research on individuals from whom it is not possible to obtain consent, including proxy or advance consent, should be done only if the physical/mental condition that prevents obtaining informed consent is a necessary characteristic of the research population. The specific reasons for involving research subjects with a condition that renders them unable to give informed consent should be stated in the experimental protocol for consideration and approval of the review committee. The protocol should state that consent to remain in the research should be obtained as soon as possible from the individual or a legally authorized surrogate.

27. Both authors and publishers have ethical obligations. In publication of the results of research, the Investigators are obliged to preserve the accuracy of the results. Negative as well as positive results should be published or otherwise publicly available. Sources of funding, institutional affiliations and any possible conflicts of interest should be declared in the publication. Reports of experimentation not in accordance with the principles laid down in this Declaration should not be accepted for publication.

**C. ADDITIONAL PRINCIPLES FOR MEDICAL RESEARCH COMBINED WITH MEDICAL CARE**

28. The physician may combine medical research with medical care, only to the extent that the research is justified by its potential prophylactic, diagnostic or therapeutic value. When medical research is combined with medical care, additional standards apply to protect the subjects who are research subjects.

29. The benefits, risks, burdens and effectiveness of a new method should be tested against those of the best current prophylactic, diagnostic, and therapeutic methods. This does not exclude the use of placebo, or no treatment, in studies where no proven prophylactic, diagnostic or therapeutic method exists.

30. At the conclusion of the study, every subject entered into the study should be assured of access to the best proven prophylactic, diagnostic and therapeutic methods identified by the study.

31. The physician should fully inform the subject which aspects of the care are related to the research. The refusal of a subject to participate in a study must never interfere with the subject-physician relationship.

32. In the treatment of a subject, where proven prophylactic, diagnostic and therapeutic methods do not exist or have been ineffective, the physician, with informed consent from the subject, must be free to use unproven or new prophylactic, diagnostic and therapeutic measures, if in the physician's judgment it offers hope of saving life, re-establishing health or alleviating suffering. Where possible, these measures should be made the object of research, designed to evaluate their safety and efficacy. In all cases, new information should be recorded and, where appropriate, published. The other relevant guidelines of this Declaration should be followed.

**＊FOOTNOTE:** **Note of Clarification on Paragraph 29 of the WMA Declaration of Helsinki**

The WMA hereby reaffirms its position that extreme care must be taken in making use of a placebo-controlled trial and that in general this methodology should only be used in the absence of existing proven therapy. However, a placebo-controlled trial may be ethically acceptable, even if proven therapy is available, under the following circumstances:

Where for compelling and scientifically sound methodological reasons its use is necessary to determine the efficacy or safety of a prophylactic, diagnostic or therapeutic method; or

Where a prophylactic, diagnostic or therapeutic method is being investigated for a minor condition and the patients who receive placebo will not be subject to any additional risk of serious or irreversible harm.

**APPENDIX V**

**Criteria for Severe Malaria/Danger Signs**

**Severe Malaria**

- Unarousable coma *(if after convulsion, > 30 min)*
- Repeated convulsions *(> 2 within 24 h)*
  - Severe anaemia *(Hb < 5.0 g/dL)*
  - Respiratory distress *(laboured breathing at rest)*

**Danger Signs**

- Recent convulsions *(1-2 within 24 h)*
- Altered consciousness  *(confusion, delerium, psychosis)*
- Lethargy
  - Unable to drink or breast feed
  - Vomiting everything
  - Unable to stand/sit due to weakness

**APPENDIX VI. PARTICIPANT SELECTION AND ENROLLMENT**

Children attending Health Facility (HF) aged between 3 and 59 months with history of recent fever

Send to laboratory

Screening thick blood smear

Negative smear or parasitaemia > 2000 < 200,000 parasites/µl

< 2,000 or > 200,000 /µl

Refer patient to clinician

Refer patient back to HF

No information collected

Complete Screening Form

Excluded Passed Initial Screening

Complete Informed Consent Form

Excluded

Refer patient back to HF

Save screening form only

Assign Study Number

Complete Case Report Forms

Refer to the Laboratory

Hb < 5.0 g/dl

Refer to the Investigator/Study Nurse

Admit at the clinic or manage as outpatients for 3 days

If a more carefull reading of the day 0 blood slide shows that parasite density outside required range: protocol violation. Continue follow up

Continue with scheduled follow-up.

**APPENDIX VII. PARTICIPANT SCREENING FORM**

**STUDY SITE CODE:________ SCREENING NUMBER: ________________**

SCREENING FORM

| **1. Names:** | **2. Date: *(dd/mm/yy)*** | **3.Weight (kg):** |
| --- | --- | --- |
| **4. Age: _________________months.** | **5. Gender: M _______ F_______** | |

| **SCREENING selection criteria**  ***Patients who are > 6 months of age and have a positive screening thick blood smear.*** | | |
| --- | --- | --- |
| **inclusion criteria** | **yes** | **NO** |
| 6. Fever (> 37.5C) or history of fever in previous 24 hours |  |  |
| 7. Weight > 5 kg |  |  |
| 8. Ability to participate in 42-day follow-up. |  |  |
| **EXCLUSION CRITERIA** | **NO** | **YES** |
| 9. Participating in any investigational drug study during the previous 30 days? |  |  |
| 10. History of serious side effects to study medications  *If present, indicate drug / side effect:*   ________________________   __________________________   ________________________ |  |  |
| 11. Evidence of severe malaria / danger signs  *If “ YES” indicate criteria. If “NO”, leave blank.*   Unarousable coma *(if after convulsion, > 30 min)*   Repeated convulsions *(> 2 within 24 h)*   Severe anaemia *(Hb < 5.0 g/dL)*   Respiratory distress *(laboured breathing at rest)*   Recent convulsions *(1-2 within 24 h)*   Altered consciousness*(confusion, delerium,,psychosis)*   Lethargy   Unable to drink or breast feed   Vomiting everything   Unable to stand/sit due to weakness |  |  |
| 12. Evidence of concomitant febrile illness  *If “YES”, indicate illness. If “NO”, leave blank.*   Pneumonia/RTI  Measles   Otitis Media  UTI   Gastroenteritis  Other:_________________ |  |  |
| **INCLUSION CRITERIA** | **YES** | **NO** |
|  |  |  |
| 13. Provision of informed consent. |  |  |
| 14. Absence of persistent vomiting of study medications on day 0 |  |  |
| ***Complete at day 1.*** | | |
| 15. *P. falciparum* mono-infection |  |  |
| 16. Parasite density > 2000/µl and < 200,000/µl  *If “NO” specify density* < 2000/µl  > 200,000/µl |  |  |

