### Exclusion criteria

Patients with any of the following criteria will not be admitted to the study:

1. Participation in any investigational drug study during the previous 30 days.

2. Known hypersensitivity to the study drugs.

1. Severe malaria.
2. Danger signs: not able to drink or breast-feed, vomiting (> twice in 24hours), recent history of convulsions (>1 in 24h), unconscious state, unable to sit or stand.
3. ECG abnormality that requires urgent management.
4. Presence of intercurrent illness or any condition which in the judgement of the investigator would place the subject at undue risk or interfere with the results of the study.
5. Severe malnutrition (defined as weight for height <70% of the median NCHS/WHO reference.
6. Ongoing prophylaxis with drugs having antimalarial activity such as cotrimoxazole for the prevention of Pneumocisti carini pneumonia in children born to HIV+ women.

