# PATIENT WITHDRAWAL CRITERIA

During the study, the following conditions are reasons **for stopping the study treatment and/or for excluding the patients from further efficacy assessments:**

1. Any treatment failure (including early failures);

2. Withdrawal of informed consent;

3. Use of antimalarial drugs (or antibiotics with antimalarial activity) outside of the study protocol;

4. Persistent vomiting of study drugs **on Day 0**  (at least twice the same dose);

5. Failure to complete the study treatment

6. Investigator's request for safety reasons (for example, onset of serious adverse events, necessitating study interruption);

6. Lost to follow-up (unable to locate the patient) before Day 28.

Patients with one or more of the conditions listed above will have to be followed-up for the safety assessment until Day 42

These reasons for premature withdrawing will be referred to Day 28 (primary evaluation time).

The reasons for withdrawing between Day 29 and Day 42 will also be recorded in the study CRF.

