## Population Analysed

The following populations will be considered for the statistical analysis of efficacy.

**Intention-to-Treat (ITT) Population**. Defined as all randomized patients who will take at least one dose of the study treatment. All patients who withdrew from the study for one of the reasons listed in section 5 as well as the patients for whom the PCR is not interpretable or missing will be evaluated as failures. For the robustness analyses, these patients will be evaluated in different ways in this population (see section 9.2).

**Modified Intention-to-Treat (modified ITT) Population**. Defined as the ITT population with the exclusion of the lost-to-follow-up patients before Day 28 for unknown reasons (non informative drop-outs). More specifically, patients withdrawing from the study for reason 7 (see section 5) will be excluded, while all other withdrawals will be counted as failures (these reasons might be potentially considered correlated with lack of efficacy, i.e. are referred to as informative drop-outs). The patients for whom the PCR is not interpretable or missing will be assigned the result “recrudescence” or “re-infection” according to the ratio between these outcomes which was observed among the evaluable PCRs within each treatment group. This rule about PCR will be applied for the primary analysis. For all analyses for which the knowledge of the outcome is needed for each patient individually (for example, the Breslow Day test or the logistic regression or the analyses where a baseline covariate is needed), different scenarios will be considered, i.e. the most two extreme ones of considering all patients with not interpretable or missing PCRs as failures or as successes and the intermediate one of excluding them all.

**Per-Protocol (PP) Population**: defined as all randomized patients who will be eligible according to the study protocol, will receive at least 80% of the study medication, will have the Day 28 assessment, will not take other anti-malarial drugs and, in case of the presence of asexual parasite stages on thick or thin blood smears, will have an evaluable PCR. The protocol violations listed below will also be considered reasons for excluding the patients from this population:

 failure to attend a follow-up visit on Days 0-2 and patient cannot be located within 6 hours of scheduled time;

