***If any of the responses fall into the shaded area, exclude the patient from the study***

**APPENDIX VIII. CRITICAL STEPS**

**Days 0 and 1**

Evaluate patient and complete Case Report form. Administer study medications.

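### The Appendix VII screening form applies an exclusion instruction to checks made after randomisation and first dose, contradicting sections 5, 6 and 9.1 and Appendix VI

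*Combined protocol and SAP*

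**What the plan says.** **The form.** Appendix VII places "Absence of persistent vomiting of study medications on day 0" (item 14) among its YES/NO inclusion criteria. Items 15 and 16, on mono-infection and parasite density, follow the line "Complete at day 1". The instruction after the table is "If any of the responses fall into the shaded area, exclude the patient from the study".

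**The body of the protocol.**
- Section 5, reason 4, lists "Persistent vomiting of study drugs" on Day 0 as a reason for stopping treatment and/or further efficacy assessment. Safety follow-up continues to Day 42.
- Section 9.1 defines ITT as every randomised patient with at least one dose. Section 5 withdrawals are failures there. Modified ITT drops only those lost to follow-up before Day 28, "while all other withdrawals will be counted as failures".
- Section 6 treats any eligibility violation as a protocol violation. It keeps the child in efficacy and safety follow-up and in ITT, and removes the child only from what it calls the Evaluable population.
- Appendix VI says, where a closer reading of the Day 0 slide finds "parasite density outside required range: protocol violation. Continue follow up".

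**Two further mismatches.** The Appendix VI flowchart starts from children "aged between 3 and 59 months with history of recent fever", while section 3.7.1 starts at 6 months. Section 3.7.2 excludes for "recent history of convulsions (>1 in 24h", while Appendix V and item 11 of the form list one or two convulsions in 24 hours as a danger sign.

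**The concern.** Keeping the study drug down is an outcome of treatment, so it cannot serve as an entry criterion. Section 9.1 recognises this by counting such children as failures. A site that works from the form may instead treat them as never enrolled.

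The trial is open label. Under section 3.13, Day 0 has one administration of DHA+PPQ and two of A+L, so equal vomiting in the two arms cannot be assumed. Non-inferiority must be shown in both modified ITT and Per Protocol. The Per-Protocol set requires at least 80% of the medication and a Day 28 assessment, so persistent vomiters will generally be absent from it anyway. Modified ITT is therefore the co-primary set in which these failures count.

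For items 15 and 16 the stake is different. These children should contribute an observed Day 28 outcome to ITT and modified ITT, and Day 42 safety data. If the site stops following them, those data cannot be recovered later.

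**Working it through.** **Step 1: order of events.** Section 3.1 conceals allocation until screening and recruitment are complete. Visit 1 in section 3.8 is both the screening visit and the first administration. A child can vomit study medication only after receiving it, and Day 1 comes after the first dose. Items 14 to 16 are therefore all answered in randomised, dosed children.

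**Step 2: the rules side by side.**

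| Finding | Appendix VII | Rest of the protocol |
| --- | --- | --- |
| Persistent Day 0 vomiting (item 14) | Exclude | Section 5: withdrawal, safety follow-up to Day 42. Section 9.1: failure in ITT and modified ITT |
| Not a mono-infection (item 15) | Exclude | Section 6: violation of an eligibility criterion, follow-up continues, stays in ITT |
| Density out of range (item 16) | Exclude | Section 6 as above; Appendix VI says the same for density |

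Section 5 prints the number 6 twice. The reason 7 that section 9.1 removes from modified ITT is the last item, loss to follow-up. Vomiting, reason 4, is not removed.

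**Step 3: the plan's own power figures.** Section 3.4.1 gives about 83% (modified ITT) and 82% (Per Protocol). Take power = Phi[(0.05 - c)/SE - 1.96], with c = 0.5(1/nT + 1/nC) and SE unpooled.
- Modified ITT, 10% attrition, 900 and 450, cure 0.91: SE = sqrt(0.0819/900 + 0.0819/450) = 0.01652; c = 0.00167; power = Phi(2.925 - 1.96) = 83.3%.
- Per Protocol, 30% attrition, 700 and 350, cure 0.93: SE = sqrt(0.0651/700 + 0.0651/350) = 0.01670; c = 0.00214; power = Phi(2.865 - 1.96) = 81.7%.

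Both agree with the plan. No stated figure is wrong on this point.

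**Step 4: what removing vomiters would do.** The vomiting rates are assumptions, because the documents give none. Let both arms have 91% cure with vomiters counted as failures, so the true difference is 0. Removing a fraction v from an arm changes its rate to 0.91/(1 - v).

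| Vomiting, DHA+PPQ v A+L | Rates after removal | Difference |
| --- | --- | --- |
| 3% v 1% | 0.91/0.97 = 93.8% v 0.91/0.99 = 91.9% | +1.9 points |
| 1% v 3% | 91.9% v 93.8% | -1.9 points |
| 2% v 2% | 0.91/0.98 = 92.9% in both | 0 |

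**Step 5: error rate at the margin.** Set the true difference, vomiters counted, to exactly -5 points (86% v 91%), with 900 and 450 patients and the Step 3 formula. The chance of wrongly meeting the margin is 2.0% when vomiters count as failures.
- Removed at 3% v 1%: 0.86/0.97 - 0.91/0.99 = -3.3 points, and the chance is 15.3%.
- Removed at 1% v 3%: 0.86/0.99 - 0.91/0.97 = -6.9 points, and the chance is 0.05%.
- Removed at 2% v 2%: 0.86/0.98 - 0.91/0.98 = -5.1 points, and the chance is 1.7%.

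Steps 4 and 5 assume that every persistent vomiter is lost from the analysis, which is the extreme case.

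**The case against.** The strongest reply is that section 9.1 already settles the analysis. A child who vomits the Day 0 dose has been randomised and dosed, so belongs to ITT and modified ITT as a failure. Nothing in Appendix VII redefines either set. The form's word for exclusion could even be read as section 5's exclusion from further efficacy assessment. This reply stands. A reader might infer that the form turns failures into non-patients in the primary analysis, but the documents do not support that as a stated rule. It would happen only if sites recorded these children as screening exclusions and the record were not corrected.

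Other stronger readings also fail:
- **That the bias favours DHA+PPQ.** No vomiting rates are given, and the sign reverses when the assumed rates are swapped.
- **That items 15 and 16 bias the comparison in the same way.** Species and Day 0 density are baseline properties, not effects of treatment. The loss there is of follow-up data.
- **That the form has the wrong age.** The form itself refers to children above 6 months. Only the Appendix VI flowchart has 3 months, and that describes who is sent for a screening smear.
- **That a child entering with one convulsion is automatically an early treatment failure.** Section 3.2 requires danger signs to develop, so a convulsion before entry does not clearly qualify. The counts still disagree.
- **That the remedy is to forbid any exclusion after the first dose.** That would clash with section 5, which itself ends efficacy assessment for some children.

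The shading is also inferred: NO to items 14 to 16 is taken as shaded because they are laid out as YES/NO inclusion criteria. This is the natural reading, but the printed form should be checked.

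**Conclusion.** The contradiction is real and should be corrected. Appendix VII attaches an exclusion instruction to three items that can be answered only in randomised, dosed children. Sections 5, 6 and 9.1 and Appendix VI prescribe something else for each of them. The analysis sets as defined in section 9.1 are not altered. What is at risk is their completeness: Day 28 outcomes for children failing the Day 1 slide check, Day 42 safety data for all of them, and possibly vomiting failures in modified ITT.

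For vomiting the loss could differ by arm, in a direction and size that the documents do not allow one to state. The 1.9-point shift, in either direction, rests on assumed rates of 3% and 1% and on complete removal. With equal rates it is nil when the true difference is zero. Sample size and stated power are unaffected.

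**What to change.** Reconcile Appendix VII with sections 5, 6 and 9.1:
- Take items 14 to 16 out of the form's exclusion logic. Record item 14 under section 5, reason 4, and items 15 and 16 as section 6 protocol violations.
- State that no randomised child who took a dose is removed from ITT or modified ITT because of the form, and that follow-up proceeds as sections 5 and 6 specify for each category.
- Check whether any dosed child has already been logged as a screening exclusion, and restore that child to the proper category.

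Separately, reconcile the Appendix VI age range (3 to 59 months) with section 3.7.1 (6 to 59 months), and the convulsion count in section 3.7.2 with Appendices V and VII. Which clinical limit applies, and how vomiting is managed, is for the sponsor and investigators to settle; this review takes no position.

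The cost is revised appendix forms and a memo to the five sites. No sample size, endpoint or analysis method changes.
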